### Study procedures

We will recruit 250 young people from CAMHS and private ADHD clinic lists, from the Consent for Contact (C4C) NHS Clinical Record Interactive Search (CRIS) database of patients [44], social media, the ADHD information service charity ADDISS, and through schools and youth clubs. The flow of participants through the study, including reasons for not participating in the study, will be documented in a flowchart (Fig. 1). The schedule of events is available in Table 2.

**Table 2 Tab2:** Schedule of events for ART-transition

Month	0		1	2	3	4	5	6	7	…	24
Assessment	1	2									
Baseline assessments											
Study explanation^a^	X										
Informed consent^a^	X										
Introductory training^a^		X									
ADHD diagnostic interview (DIVA-5)^a^	X										
IQ and short-term memory WASI-II and WAIS-IV^a^	X										
Cognitive tasks (CPT/GNG and fast track)^a^		X									
‘About You’: Socio-demographics, medical history, service use, experience with Technology, life experiences^a,b^	X										
Autism Spectrum Disorder (AQ-10)^a,b^	X										
DNA saliva sample^a^		X									
Remote data collection											
Fitbit Charge HR6: Physical activity, sleep, heart rate, breathing rate and skin temperature^c^			Continuous (months 1–24)								
Passive App (smartphone sensors: relative location, light, smartphone use, battery life)^c^			Continuous (months 1–24)								
Medication use^d^			Daily (months 1–24)								
ADHD symptoms^d^			Daily (months 1–24)								
Medication side effects (CADDRA)^d, e^			XXXX	XXXX	XXXX	XXXX	XXXX	XXXX	XXXX	XXXX	XXXX
ADHD (BAARS-IV and functional impairment scale-self)^d^		X	X	X	X	X	X	X	X	X	X
Anxiety (GAD-7)^d^		X	X	X	X	X	X	X	X	X	X
Depression (PHQ-8)^d^		X	X	X	X	X	X	X	X	X	X
Aggression (RPQ-A)^d^		X	X	X	X	X	X	X	X	X	X
Irritability (ARI - self)^d^		X	X	X	X	X	X	X	X	X	X
Smoking (Test Fagerstrom)^d^		X	X	X	X	X	X	X	X	X	X
Alcohol use (AUDIT)^d^		X	X	X	X	X	X	X	X	X	X
‘About You’ – remote version^d^			X	X	X	X	X	X	X	X	X
Speech sample task^d^		X	X	X	X	X	X	X	X	X	X
ADHD (BAARS-IV and functional impairment scale–informant report)^b^		X	X	X	X	X	X	X	X	X	X
Irritability (ARI – informant report)^b^		X	X	X	X	X	X	X	X	X	X
Cognitive tasks (CPT/GNG and fast task)		X						X			X
Self-esteem (Rosenberg self-esteem scale)^d^		X						X			X
Eating behaviours (EDE-QS)^d^		X						X			X

^a^With researcher

^b^REDCap web-based platform

^c^RADAR-base Passive App

^d^RADAR-base Active App

^e^Delivered four times per month (every week)

Recruitment through clinical and private CAMHS teams involves the clinical teams contacting relevant individuals by their preferred method of contact (post, email, or telephone) and providing them with information about the study. If they consent for their details to be passed onto the research team, the research team will contact the patient and provide them with further information. If the patient is interested in participating, the first baseline assessment with the research team will be scheduled.

The baseline assessments take approximately four hours to complete across two days, with approximately a week between sessions. The virtual baseline sessions consist of (1) the Diagnostic Interview for ADHD in Adults (DIVA [45] to have a record of current ADHD symptoms and clinical impairment (2), a brief IQ and short-term working memory test [46, 47] (3) two baseline questionnaires: a demographic About You questionnaire and the Autism Spectrum Quotient questionnaire (AQ-10 [48]), (4) two cognitive tasks of the Combined Cued Continuous Performance Test and Go/NoGo (CPT/GNG) task and the Fast Task (while researcher present) [24], (5) completion of questionnaires (see Table 2) (6), a training session on the smartphone and wearable device, and (7) guidance on how to collect DNA saliva sample (optional). Participants are able to take breaks during the sessions if required. During the baseline sessions, the participants are also asked to identify a partner, a family member or a close friend who could complete informant report versions of the active monitoring questionnaires on ADHD symptoms, impairment, and irritability. The participants are asked to forward an email to their chosen informant, which asks the informant to get in touch with the research team if they are happy to participate. If the informant consents to participation, they will be sent online questionnaires using the REDCap web-based platform.

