## Background

Late adolescence and the transition to adulthood is a highly challenging period for young people with attention deficit hyperactivity disorder (ADHD) that can lay the foundations for diverging adulthood trajectories. Many of the conditions that frequently co-occur with ADHD, such as depression, delinquency and substance misuse, often emerge in adolescence [1–3]. Major life transitions at this age, such as leaving education, starting work or moving out of the parental home, lead to multiple new demands and changes in available support networks, further increasing the vulnerability of young people with ADHD. This vulnerable phase coincides with the clinical transition from child and adolescent mental health care to adult services, which itself is a focus of major current clinical concern: UK data show that a large proportion of young people with ADHD do not successfully transfer to adult services, despite significant needs for ongoing treatment [4].

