### Study population

The sample sizes were determined by simulation and analytical methods. For Aim 1, we considered power to detect associations between pairs of variables (e.g., ADHD symptoms and digital markers), provide precise of estimates of within-person variance and intraclass correlation (ICC), and the impact of missing data. For Aim 2, we estimated the sample size needed to develop multivariable prediction models (based on an expected model performance of R² ≈ 0.5 and 20 model parameters). Full details are provided in the Supplementary Materials. Overall, a sample of 250 participants (each providing monthly outcome assessments and continuous RMT data collection) will be sufficient to detect associations and estimate within-person variance with precision (Aim 1), even under conservative assumptions about missing data. This sample will be adequate to develop multivariable prediction models. Table 1 summarises the study eligibility criteria.

**Table 1 Tab1:** Eligibility criteria for participation in ART-transition

Participant inclusion criteria	1	Diagnosis of DSM-5 ADHD
	2	Aged 16–17
	3	Able to give informed consent for participation
	4	Willing and able to complete self-reported assessments via smartphone
	5	Willing to use either their own compatible Android phone or a study Android phone as their only smartphone during the data collection period
	6	Willing to wear the wearable device (Fitbit) during the data collection period
Participant exclusion criteria	1	Psychosis, currently experiencing a major depressive episode, mania, drug dependence in the last six months, or a major neurological disorder
	2	Recent contact with psychiatric acute care (admission, crisis team or liaison team (A&E)) in the last six months
	3	Any other major medical disease which might impact upon the patient’s ability to participate in normal daily activities (e.g., due to hospitalisations)
	4	Pregnancy
	5	IQ < 70
Informant inclusion criteria	1	A parent or guardian, as chosen by the participant with ADHD
	2	Aged 18 or over
	3	Willing and able to complete web-based questionnaires regarding the participant with ADHD

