Participants are asked to report their medication use side effects weekly using the CADDRA Patient ADHD Medication form [49]. This form contains four items on changes experienced since starting medication and 28 items on side effects. Every four weeks, participants are asked to complete a longer set of questionnaires: ADHD symptoms and impairments will be measured using the Barkley Adult ADHD Rating scale on current symptoms (BAARS-IV) [50] and Barkley ADHD functional impairment scale [51]. This includes the 18 diagnostic ADHD symptoms and 10 items on functional impairment. Depression is measured using the 8-item Personal Health Questionnaire Depression Scale (PHQ-8 [52]), which is a widely used measure of current depression in the general population; anxiety is measured using the 7-item Generalized Anxiety Disorder questionnaire (GAD-7 [53]), which provides a dimensional score of anxiety symptoms; aggression is measured using the 23-item Reactive-Proactive Aggression Questionnaire for Adults (RPQ-A [54]); irritability is measured using the self-reported 7-item Affective Reactivity Index questionnaire (ARI-s [55]); smoking behaviours are measured using the 6-item Test Fagerstrom questionnaire [56]; and alcohol use is measured using the Alcohol Use Disorders Identification Test (AUDIT [57]). In addition, participants are asked to complete a remote monitoring version of the “About you” questionnaire, which includes questions on changes to life circumstances, life events, medication use, and other ADHD-related and non-ADHD-related treatments. Every six months, participants are asked to complete two further questionnaires. Positive and negative feelings about the self are measured using the 10-item Rosenberg Self-Esteem Scale [58], and eating disorder symptoms are measured using the 12-item Eating Disorder Examination Questionnaire (EDE-QS) [59].

Participants are asked to complete a short speech task every four weeks on the Active App. They also self-administer the two cognitive tasks of CPT/GNG and Fast task four times during the 24 months (months 6, 12, 18, and 24) on their home PC or laptop, without the researcher present. In addition, ratings on ADHD symptoms are obtained monthly from a partner, a family member, or a close friend of the individual with ADHD using the web-based REDCap.

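### Monthly informant ratings span the months in which participants may leave home, with no described measure of how much the informant sees them, so changed observation could be mistaken for change in the informant-rated scores

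*Protocol article*

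**What the plan says.** **Instruments and schedule.** Under Study procedures, Table 2 lists "ADHD (BAARS-IV and functional impairment scale–informant report") and "Irritability (ARI – informant report") at baseline and in every month to month 24. That is 25 scheduled occasions per scale (1 + 24), all through REDCap. The text of that section describes the informant as someone "who could complete informant report versions of the active monitoring questionnaires on ADHD symptoms, impairment, and irritability".

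**Who the informant is.** The document gives two answers.
- Table 1 (Study population) admits as informant "A parent or guardian, as chosen by the participant with ADHD".
- Study procedures states that "the participants are also asked to identify a partner, a family member or a close friend", and the Active app section says that "ratings on ADHD symptoms are obtained monthly from a partner, a family member, or a close friend of the individual with ADHD".

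**Expected transitions.** The Background refers to "Major life transitions at this age, such as leaving education, starting work or moving out of the parental home". Participants enter at 16 or 17 and are followed for 24 months, so they finish at 18 or 19.

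**What is recorded about circumstances.** The remote About You form (Active app section, every four weeks) is completed by the participant and covers altered life circumstances and life events. Contact between informant and participant is not mentioned for this form or for the informant form.

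**Analysis.** For Aim 1 the Analysis plan specifies mixed models, spline-based random slopes and lagged associations that separate within- from between-person effects. It does not say which rater defines symptoms, impairment or irritability, and it has no term for informant contact.

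**The concern.** An informant score reflects both the young person's behaviour and how much of it the informant sees. If a participant leaves home and the informant stays behind, the second part can drop from daily observation to occasional observation while the form stays the same. The score may then move with no change in the young person.

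The timing makes this more than ordinary measurement noise. The loss of observation would coincide with one of the life transitions the study sets out to examine. If informant scores are used for objectives 1a or 1b, a move could appear to precede a change in symptoms, impairment or irritability because of the measurement alone. That finding could then feed the Aim 2 predictors and the Aim 3 app targets.

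It would also add a time-varying component to the disagreement between self and informant, which the Background already describes as limited. These forms are the only repeated ratings by another person, because the diagnostic interview takes place only at baseline. Contact that is not recorded month by month cannot be reliably reconstructed later.

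**Working it through.** The plan states no figure on this point, so there is none to reproduce. The check is a structural argument followed by an illustration.

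**1. Does the within-person model remove the problem?** Write the informant score of person i in month t as

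Y(i,t) = a(i) + θ(i,t) + δ·L(i,t) + e(i,t)

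Here a(i) is the stable level, θ is true change, L = 1 in months when the informant has lost sight of the participant, and δ is the resulting shift in the score.

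Centring on the person's own mean removes a(i) and leaves δ·[L(i,t) − mean of L(i)]. Let M = 1 after a move. If L switches on with M, the within-person coefficient on M estimates the true effect plus δ. If only a fraction c of moves bring a loss of sight, the bias is c·δ. The same holds for lagged terms, because L persists after the move. Separating within- from between-person effects protects against stable differences between informants. It does not protect against a change that arises with the event. More monthly forms narrow the interval around the biased value but do not reduce the bias.

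**2. How large might it be?** With no true change, the spurious mean change from baseline to month 24 is

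m × c × δ

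where m is the share of participants who have moved by month 24. The documents give none of these three quantities. The values below are assumptions: m from 10% to 60%, δ from 0.1 to 0.5 SD, and c = 1 (every mover's informant loses sight).

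| m | δ = 0.1 SD | δ = 0.3 SD | δ = 0.5 SD |
|---|---|---|---|
| 10% | 0.01 | 0.03 | 0.05 |
| 30% | 0.03 | 0.09 | 0.15 |
| 50% | 0.05 | 0.15 | 0.25 |
| 60% | 0.06 | 0.18 | 0.30 |

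For example, 0.30 × 1 × 0.3 SD = 0.09 SD. The range is 0.01 to 0.30 SD. Among movers whose informant loses sight, the shift is the full δ, 0.1 to 0.5 SD.

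**3. What does the unclear informant identity do to this?** Under Table 1 the informant is a parent or guardian, and for a move out of that person's home c may be close to 1. Under the other two sections a partner or friend may rate, and that person may see the participant less, equally or more after the move. Then c falls, or shifts of opposite sign partly cancel. With c = 0.5 every table entry halves, so 0.09 becomes 0.045 SD. The problem does not disappear under either reading, but its size and sign cannot be fixed until the sections agree.

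**The case against.** Several points on the other side stand.

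- **The informant need not be a parent.** A reader of Table 1 might infer that all these ratings come from a parent who is left behind. Study procedures and the Active app section say otherwise, so that reading is not secured. What remains is that any informant's contact can change around a move and that neither version is described as recording it.
- **No rater is named in the analysis.** A reader might infer that lost observation will be reported as symptom change. The text does not support that. Self-report versions of all three measures run on the same schedule, the Background presents informant ratings as one source among several, and objective 1e is devoted to digital and cognitive markers. The most one can say is that informant scores, if analysed for change, could mislead.
- **Moves are partly captured.** The About You form asks about life circumstances, so it is not true that nothing bears on co-residence. It is a proxy reported by the participant, however, and it does not measure how much the informant sees.
- **The article is condensed.** The items on the informant form are not reproduced, and a contact item may exist. Its absence is established only for this text. What contact data to collect is nevertheless a matter of data collection and cannot be left to the analysis stage.
- **The magnitude is assumed.** Any calculation that puts in a shift for movers gets the same shift back, so showing that such a shift would reach significance adds no evidence that it occurs.
- **Restricting the main analysis to high-contact months would do harm.** It conditions on a consequence of moving and discards mainly the post-move months of interest. This stands, and the fix avoids it.

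**Conclusion.** The concern holds in limited form. The described informant data cannot distinguish a change in the participant from a change in what the informant sees, and the planned within-person modelling does not repair this. Only the informant-rated measures are exposed. Self-ratings, digital markers and cognitive tasks are not affected by this mechanism.

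The direction is unknown. The size, about 0.01 to 0.3 SD in the mean with the full assumed shift of 0.1 to 0.5 SD among movers who lose observation, runs from negligible to material. It rests wholly on the assumed share of movers, the assumed shift and c = 1. The documents support neither a claim that bias will occur nor one that it is large. They do support recording contact while that is still possible. This is a cheap improvement, not an error that undermines the study.

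**What to change.** 1. **Reconcile the informant definition.** Table 1, Study procedures and the Active app section should state the same eligible informants.
2. **Add one item to the monthly REDCap informant form**, unless the full form already has it: whether the informant lived with the participant in the rated period, and on how many days they were in contact.
3. **Analyse informant scores separately from self-report.** Keep all months in the main informant analysis. Report results alongside it with contact as a time-varying term, plus a sensitivity analysis limited to months that meet a preset minimum of contact. Contact may itself respond to symptoms or to the move, so neither supplementary result should simply replace the main one. They should be read together.
4. **For forms already collected**, use the life-circumstance items in About You as a proxy for co-residence and state that they do not measure contact.
5. **Interpretation.** Treat a shift in informant score at a move as inconclusive unless it is also seen where contact stayed constant.

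The cost is one short item per month, some analysis wording, and wider intervals in the contact-restricted sensitivity analysis. The main informant analysis loses no months.

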**Fig. 1 Fig1:**
[figure not shown]
Participant flowchart

### Remote data collection

Remote monitoring begins immediately after the two baseline assessments and lasts for 24 months. The remote monitoring consists of both active and passive components, following procedures established for the wider ART research programme, and is linked to the RADAR-base mobile-health platform [28]. Below is a summary of the methods of remote data collection used in the ART-transition study (Fig. 2).

**Fig. 2 Fig2:**
[figure not shown]
Remote monitoring system for ART-transition: passive and active data flows

#### Compatible android smartphone

The RADAR-base Passive App requires the use of an Android phone running the Android 10 operating system or newer. Participants without a suitable smartphone are provided with a compatible Android device. If this requirement creates a significant barrier to recruitment, we will consider relaxing the inclusion criteria of “*Willing to use either their own compatible Android phone or a study Android phone as their only smartphone during the data collection period”* to allow a subset of participants to retain their iPhone if they do not wish to switch to an Android phone. These participants will thus not download the Passive App.

#### Active app

Participants are asked to download the RADAR-base Active App, which asks the participant to complete questionnaires at specific intervals. Participants are asked to complete two short questionnaires every day. The first is a single-item questionnaire assessing the impact of their ADHD symptoms on that day, rated on a scale of 1–5. The second is for medication use. If participants are on medication for ADHD, they are asked if they took their medication that day, with follow-on questions on the type and dose of medication or why medication was not taken (e.g., experienced side effects, forgot to take their medication, or chose not to take their ADHD medication that day). If participants indicate at baseline or in the remote monitoring period that they do not currently take medication, this questionnaire will be paused for one month before asking them again if they are currently taking ADHD medication.

Participants are asked to report their medication use side effects weekly using the CADDRA Patient ADHD Medication form [49]. This form contains four items on changes experienced since starting medication and 28 items on side effects. Every four weeks, participants are asked to complete a longer set of questionnaires: ADHD symptoms and impairments will be measured using the Barkley Adult ADHD Rating scale on current symptoms (BAARS-IV) [50] and Barkley ADHD functional impairment scale [51]. This includes the 18 diagnostic ADHD symptoms and 10 items on functional impairment. Depression is measured using the 8-item Personal Health Questionnaire Depression Scale (PHQ-8 [52]), which is a widely used measure of current depression in the general population; anxiety is measured using the 7-item Generalized Anxiety Disorder questionnaire (GAD-7 [53]), which provides a dimensional score of anxiety symptoms; aggression is measured using the 23-item Reactive-Proactive Aggression Questionnaire for Adults (RPQ-A [54]); irritability is measured using the self-reported 7-item Affective Reactivity Index questionnaire (ARI-s [55]); smoking behaviours are measured using the 6-item Test Fagerstrom questionnaire [56]; and alcohol use is measured using the Alcohol Use Disorders Identification Test (AUDIT [57]). In addition, participants are asked to complete a remote monitoring version of the “About you” questionnaire, which includes questions on changes to life circumstances, life events, medication use, and other ADHD-related and non-ADHD-related treatments. Every six months, participants are asked to complete two further questionnaires. Positive and negative feelings about the self are measured using the 10-item Rosenberg Self-Esteem Scale [58], and eating disorder symptoms are measured using the 12-item Eating Disorder Examination Questionnaire (EDE-QS) [59].

Participants are asked to complete a short speech task every four weeks on the Active App. They also self-administer the two cognitive tasks of CPT/GNG and Fast task four times during the 24 months (months 6, 12, 18, and 24) on their home PC or laptop, without the researcher present. In addition, ratings on ADHD symptoms are obtained monthly from a partner, a family member, or a close friend of the individual with ADHD using the web-based REDCap.

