### Study objectives

This project, ADHD Remote Technology and ADHD transition: predicting and preventing negative outcomes (ART-transition), will use RMT in adolescents with ADHD to collect unobtrusive, real-world data over 24 months. By recruiting 250 16-17-year-olds with ADHD and monitoring them remotely, we can address the following three main aims: Aim 1) To identify, with precision, the nature and timing of the real-world changes that take place in the transition to adulthood; Aim 2) To identify what predicts such changes; and Aim 3) To use the timeframes and intervention targets identified in Aims 1–2 to co-design, with young people with ADHD, a prototype for a new ADHD-transition interactive smartphone app.

Aim 1 incorporates five objectives: To identify changes in (1a) ADHD symptoms and functional impairment; (1b) new co-occurring psychiatric symptoms that may emerge (e.g. anxiety, depression, irritability, substance use, antisocial behaviour); (1c) treatment adherence and engagement with clinical services; and (1d) healthy lifestyle behaviours (e.g. physical activity, sleep, daily structure, online lifestyle), social support and employment/ studies; and (1e) To identify objective markers – digital signals and cognitive measures – that are associated with changes in the clinical symptoms. Aim 2 focuses on the development and validation of multivariable prediction models for each of the changes (outcomes) identified in Aim 1, incorporating four objectives: To identify factors that predict changes in (2a) ADHD symptoms and functional impairment; (2b) co-occurring symptoms; (2c) treatment adherence and engagement with clinical services; and (2d) adoption of healthy lifestyle behaviours and engagement with work/studies. Information on influential predictors and their timing will feed directly into Aim 3 of developing a prototype ADHD-transition smartphone app.

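### Cognitive tasks are researcher-attended at month 0 and self-administered from month 6, so the 0-to-6-month step cannot be read as true cognitive change

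*Protocol article*

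**What the plan says.** Study procedures places the CPT/GNG and Fast Task among the baseline activities: "The virtual baseline sessions consist of" a list that includes "the Fast Task (while researcher present". Table 2 agrees. Its baseline block lists "Cognitive tasks (CPT/GNG and fast track)^a" at the second month-0 assessment, and that footnote means the researcher is present.

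The Active app section has participants repeat the tasks themselves "four times during the 24 months (months 6, 12, 18, and 24", each time "on their home PC or laptop, without the researcher present".

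Study objectives gives the purpose, as objective 1e: "To identify objective markers – digital signals and cognitive measures – that are associated with changes in the clinical symptoms". The Analysis plan describes lagged linear mixed models for pairs of variables, cognitive markers included, with within-person and between-person effects separated. It names no term for supervision or first occasion. Study design states that there is no comparison group. Background says that the pilot validated self-administered versions of the two tasks.

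Table 2 also has a cognitive-task row in its remote block, with an unfootnoted mark at month 0.

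**The concern.** The mode of administration changes once, for everyone, at the same point. The first of five cognitive occasions is attended and each later one is not. The article describes no earlier practice run, so the first occasion is also the first documented exposure. If a researcher's presence or unfamiliarity with the task moves scores, the movement appears as change between months 0 and 6. Without a control group, nothing in the data can show how much of that step is artefact.

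Two uses of the data are exposed. One is any statement about cognitive change, or any trend, that includes month 0. The other is objective 1e: if symptom scores also move after month 0 for their own reasons, two unrelated series can look linked within persons.

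**Working it through.** The article states no figure on this point, so there is none to reproduce. The inputs from it are five occasions (0, 6, 12, 18, 24 months), attendance at month 0 only, no control group, and 250 participants. The shift size d and the within-task correlation are assumptions.

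**Identifiability.** Code supervised = 1 at month 0 and 0 later; first exposure has the same code.
- Columns [1, time, supervised, first exposure]: rank 3 of 4. The two effects cannot be told apart.
- Columns [1, four occasion dummies, supervised]: rank 5 of 6. Supervision cannot be told apart from a free month-0 mean.
- Columns [1, time, month-0 indicator]: rank 3 of 3. This is estimable, but the indicator absorbs supervision, first exposure and any real departure from linearity at month 0 together.

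**False change from a baseline-only shift.** Let the month-0 mean lie d SD below the rest, with no true change.
- Months 0 to 6: d. Months 6 to 24: 0.
- Linear trend: centred times are −12, −6, 0, 6, 12, so Sxx = 144 + 36 + 0 + 36 + 144 = 360. Slope = (−12)(−d)/360 = d/30 per month, and × 24 = 0.8d.
- For d of 0.1, 0.2, 0.3 and 0.5 the false 24-month change is 0.08, 0.16, 0.24 and 0.40 SD.

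**Would it be noticed as change?** SE of the mean paired change = √(2(1 − ρ)/n). With ρ = 0.6 and n = 250 complete pairs this is √(0.8/250) = 0.057 SD, so a shift of 1.96 × 0.057 = 0.11 SD is already significant at the two-sided 5% level. For d = 0.2 the probability of declaring a change is 0.89 to 0.98 (ρ from 0.5 to 0.7), or 0.69 to 0.89 with 150 pairs.

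**Spurious association for objective 1e.** Take two series unrelated within persons, each with total SD 1 and correlation ρ between occasions, shifted at month 0 by d₁ and d₂. No occasion term is fitted. Per person, the within-person sum of squares is 4(1 − ρ) + 0.8d², and the cross-product is 0.8d₁d₂.
- ρ = 0.6, both 0.3 SD: 0.072/(1.6 + 0.072) = 0.043.
- Same, ρ = 0.5: 0.072/2.072 = 0.035. ρ = 0.7: 0.072/1.272 = 0.057.
- ρ = 0.6, cognitive shift 0.3, symptom shift 0.1 or 0.2: about 0.015 or 0.03.
- ρ = 0.6, both 0.5 SD: 0.2/1.8 = 0.11.
- No symptom shift: 0.

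With 250 × 4 = 1,000 within-person degrees of freedom, the detectable r at 80% power is tanh(2.80/√999) = 0.088, so 0.043 is about half of it. It is still not harmless. At r of 0.035 to 0.057 the expected z is r√999 = 1.10 to 1.79, which gives a false-positive rate of about 20% to 43% instead of 5%. The calculation pairs concurrent values. In a lagged model, the symptom shift would have to fall on the occasion paired with the month-0 cognitive score.

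**Cost of giving up month 0.** Months 6 to 24 alone: centred times −9, −3, 3, 9, so Sxx = 81 + 9 + 9 + 81 = 180. The variance of a linear slope doubles (360/180, complete data, independent errors). The detectable r becomes tanh(2.80/√749) = 0.102, against 0.088.

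**The case against.** The strongest reply is that the article contains no error here. It says openly how each occasion is run, and the handling of month 0 is detail that an analysis plan, not shown, may already settle. Self-administration was validated in the pilot. Baseline sessions are virtual, so the contrast is a remote researcher's presence, not laboratory against home. First-exposure effects occur in any repeated testing. No document shows that a shift exists.

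Much of this stands, and it limits the point. A reader might infer that the plan analyses all five occasions as one undifferentiated series. The Analysis plan does not say so; it is only silent. A reader might also infer that objective 1e is seriously compromised. That does not follow: the association is biased only if symptoms shift too, and the bias is then small under moderate assumptions. Nor does the problem reach contrasts among months 6, 12, 18 and 24, which share one mode.

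The confounding itself remains. It comes from the data collection that the protocol fixes, not from an omitted modelling detail. Validation of the self-administered versions supports their use, but the article does not state that attended and unattended scores are interchangeable, and validation cannot remove a first-exposure effect.

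The unfootnoted month-0 mark in Table 2's remote row could mean a second, unattended baseline run, which would weaken the supervision part. The Active app section counts only four self-administrations, all from month 6, so the mark most likely repeats the attended run. The table does not say.

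**Conclusion.** The point holds within limits. Supervision and first exposure coincide completely with month 0, so the 0-to-6-month cognitive step, and any trend that includes month 0, cannot be read as true change. The false change is d over the first interval and 0.8d as a 24-month linear trend, or 0.08 to 0.40 SD for d of 0.1 to 0.5. These values of d are assumptions. That month 0 is the first exposure is inferred from the absence of any earlier run in the article.

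For objective 1e the risk is conditional and modest: r about 0.04 when cognition and symptoms each shift by 0.3 SD at a correlation of 0.6, and none without a symptom shift. Practice effects may continue from month 6 to month 24, and nothing proposed here removes them. The point deserves a change to the analysis; the cognitive data from month 6 onwards remain usable for studying fluctuation.

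**What to change.** - Include a month-0 (attended, first-exposure) indicator in every model of cognitive change and of cognitive–symptom association, fixed before analysis. If an existing analysis plan already has such a term, cite it.
- State that the 0-to-6-month step will not be interpreted as change.
- Repeat the association analysis on months 6 to 24 only, as a sensitivity analysis. A reader might take this as equivalent to the indicator, but it is not. The indicator removes only the average shift, so a shift that differs between people, and varies with their symptoms, still acts through the month-0 deviations. Exclusion removes that as well.
- Clarify the unfootnoted month-0 mark in the remote cognitive-task row of Table 2: either it is the attended run listed twice, or it is a separate run.

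The cost is one model term and one extra analysis, with no change to data collection. Precision for a linear trend falls: slope variance doubles without month 0, and the indicator has the same effect on the mean slope because it fits the month-0 mean on its own. For associations the loss in the months 6-to-24 analysis is small, with detectable r going from about 0.088 to 0.102 with complete data.
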